### Medical and socio-demographic background data

Information about the patients’ medical background, treatment and cancer-related outcome will be obtained from the diagnosis-specific Regional Oncology Centre records and from the medical records. Details about the psychosocial support provided within the standard care group will be collected via the HES where the patients will be asked to report any contact with the social worker, psychiatrist, psychologist, psychotherapist or the hospital church. Demographic data will be obtained via project-specific questions.

### Internet use

Data on the intervention and control groups’ Internet use related to their cancer disease will be collected through project-specific questions.

### Knowledge on and use of strategies to counteract symptoms

Knowledge of the disease, common symptoms and strategies to counter symptoms will be examined in a project-specific survey. The survey will include questions about perceived knowledge and whether and to what extent the patients have used, and are using, the proposed strategies to counter current symptoms. In addition, data on each study participant’s use of educational materials, activity in the “Questions and Answers (Q&A)” section, posts in discussion forums and notes in the diary will be logged in the U-CARE portal.

### Observation points

Data will be collected at baseline and at 1, 4, 7, 10, 18 and 24 months after inclusion. For the health economic evaluation, economic data will be collected at the above time points. Data on knowledge and use of strategies as well as health economic data (EQ-5D) will be collected also 2 weeks after inclusion.

### Procedure

#### *Pilot study*

A pilot study will be carried out using the same procedures and design as in the main study (see below). An evaluation will be made after randomization of 20 participants to the study. The evaluation will be made with respect to inclusion frequency, participants’ activity in steps 1 and 2 and the proportion of patients with persistent anxiety and depressive symptoms 1 month after inclusion. If the evaluation does not give rise to changes in the study design or procedures, the pilot study will seamlessly proceed to the main study.

#### *Main study*

Eligible patients at the oncology, urology and surgery clinic will be identified and asked for informed consent at a regular visit to the clinic within 6 months after initial diagnosis or detection of disease relapse.

First, participants will be asked to answer all the study’s questionnaires via the U-CARE portal. Patients with severe depression or suicide risk (as measured by the MADRS-S, see “Data collection”) at inclusion or at the 10-month measurement will be excluded from the project and contacted via telephone by a project staff psychologist. Likewise, patients will be contacted by a psychologist if there is reason to believe that they have severe depression or are suicidal according to what they write in the forum or diary or what they post on the chat. Participants in the intervention group will have access to IS immediately after randomization. Both the intervention and the control group will receive the psychosocial support as part of the standard care at their respective clinic. Both groups will answer a set of questionnaires at observation points described in Table 1. The reference group will answer a set of questionnaires at some of the observation points. The patients will be notified by e-mail of when it is time to answer questionnaires. If they do not complete the questionnaires they will be reminded by e-mail 7 days after baseline and after 7 and 12 days after any of the observation points.

### Data processing and analysis

The end points of the study will be evaluated according to the intention-to-treat principle. In addition the complier average causal effect will be analysed. Differences between the intervention and the control group regarding anxiety, depression, post-traumatic stress, health-related quality of life and the presence and development of these variables over time will be analysed using analysis of variance (ANOVA) with repeated measurements. Should the variables not satisfy the basic assumptions of normal distribution and equal variance, the Mixed regression models will be used for analysis [43]. How and to what extent the different parts of the Internet-based system for psychosocial support are used will be analysed using the data on the study participants’ activities recorded in the system. Qualitative content analysis [44] will be used to analyse the content of the discussion forums and diaries. We also plan to use computerized text analysis. Appropriate methods to control for mass significance will be used.

For process analyses of CBT, multiple regression analysis will be used. The health economic analyses will relate to the interventions’ cost-effectiveness compared with the cost-effectiveness for standard care, which will be analysed in the way that incremental costs are related to the quality-adjusted life years (QALYs). The costs include direct costs (e.g. medical care) and indirect costs (e.g. production) as well as costs for patients, families and health care and to the community. We will analyse the differences between the groups in the short term, after 1, 4, 7, 10 months, and in the long term, after 18 and 24 months. Health economic effects will be analysed after 10 and 24 months. Background variables, such as medical and socio-demographic factors that could potentially function as moderators or confounders, will be controlled for. Internet use other than the IS will be monitored by a project-specific questionnaire administered to both groups in order to control for this potential confounder.

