## Background

### The need to identify patients with clinical levels of distress

In Sweden approximately 55,000 persons were diagnosed with cancer in 2010 [1]. Research has shown that a large proportion of patients with cancer have the ability to handle the mental strain that the disease can cause [2-4]. However, 20–30% develop anxiety and depression symptoms [5-7]. There is a need for enhanced psychosocial support for this group in order to prevent persistent psychological distress [8]. Patients with incurable disease report higher levels of anxiety and depression compared with patients who can be cured [9]. Several studies have also shown a correlation between cancer patients’ and their family’s levels of psychological distress [10].

Also, a lack of social network and a low socio-economic status, with a low educational level, low income and unfavourable working conditions, can have a negative impact on cancer patients’ psychological and physical wellbeing as well as on disease progression [11,12]. Such factors should be included as potential moderators in studies of interventions aimed at reducing psychological problems.

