### The main research questions

#### *Primary research question*

• Do participants who receive Internet-based stepped care report lower levels of anxiety and/or depressive symptoms at 10 months after randomization compared with participants receiving standard care? See details under “Statistical power” below.

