### Statistical power

The main outcome measure is the Hospital Anxiety and Depression Scale (HADS) [27]. It consists of 14 questions divided into one subscale for anxiety symptoms (seven questions) and one for depressive symptoms (seven questions). Both are 21-point scales. Values <7 points on any of the subscales indicate mild anxiety or depression. Values < 10 points indicate clinically significant levels of anxiety and depressive symptoms. A change of at least 20% on the HADS is considered to be a clinically relevant change [28]. In one previous study of patients with <7 points cut-off on any of the HADS subscales, the mean score for anxiety was 10 and for depression, 8 [6]. To achieve 80% statistical power (alpha = 0.05) needed to detect a mean difference of 2.0 points on the anxiety subscale and 1.6 points on the depression subscale, 65 patients are required in each of the intervention and control groups. Based on experience from previous intervention studies, we estimate that approximately 30% of study participants will not complete the data collection. This means that we need to include at least 95 patients in each group. For the present study, approximately 1,300 patients need to be enrolled, <300 of whom are likely to have anxiety or depression symptoms, <200 of whom can be expected to complete the study.

Patients with <7 points on any of the subscales will be allocated to a reference group and answer questionnaires at baseline and at three observation points during the time of the intervention. They will answer questionnaires that measure anxiety, depression and health-related quality of life.

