### Randomization

Participants with anxiety and/or depressive symptoms (<7 on any of the HADS subscales) will be randomized to either Internet-based stepped care or standard care. Randomization will be stratified for curable/non-curable disease and will be done in blocks.

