### Data collection

All patient-reported data will be collected through the U-CARE platform. Well-known questionnaires with good psychometric properties will be used. Table 1 presents an outline of questionnaires and observation points.

**Table 1 T1:** Summary of the study’s instruments and the observation points at which they will be used

**Instrument**	**Observation points**
HADS	At baseline and at 1, 4, 7, 10, 18 and 24 months
MADRS-S	At baseline and at 10 months
STAI-S	At baseline and at 10 months
ESSI	At baseline
NLEs	At baseline
EROS	At baseline and at 10 months
PCL-C	At baseline and at 10, 18 and 24 months
EORTC QLQ-C30	At baseline and at 1, 4, 7, 10, 18 and 24 months
EORTC QLQ-BR23^1^	At baseline and at 1, 4, 7, 10, 18 and 24 months
EORTC QLQ-PR25^1^	At baseline and at 1, 4, 7, 10, 18 and 24 months
EORTC QLQ-CR29^1^	At baseline and at 1, 4, 7, 10, 18 and 24 months
FACIT-F	At baseline and at 1, 4, 7, 10, 18 and 24 months
ISI	At baseline and at 1, 4, 7, 10, 18 and 24 months
PTGI-SF	At 10 months
Health economic questionnaire	At 1, 4, 7, 10, 18 and 24 months
EQ-5D	At 2 weeks and 1, 4, 7, 10, 18 and 24 months
Patient satisfaction questionnaire	At 1, 4 and 10 months
Internet use questionnaire	At 1, 4, 7, 10, 18 and 24 months
Knowledge and strategies questionnaire	At 2 weeks and 1 and 10 months

*EORTC QLQ* European Organization for Research and Treatment of Cancer (EORTC) Quality of Life Questionnaire, *EQ-5D* Euroqol 5D, *EROS* Environmental Reward Observation Scale, *ESSI* Enriched Social Support Inventory, *FACIT-F* Functional Assessment of Cancer Therapy: Fatigue, *HADS* Hospital Anxiety and Depression Scale, *ISI* Insomnia Severity Index, *MADRS-S* Montgomery-Åsberg Depression Rating Scale – Self-Report, *NLEs* Negative Life Events questionnaire, *PCL-C* Post-Traumatic Stress Disorder (PTSD) Checklist – civilian version, *PTGI-SF* Post-Traumatic Growth Inventory, Short Form, *QLQ-Br25* Quality of Life Questionnaire with diagnosis-specific modules for breast cancer, *QLQ-C30* Quality of Life Questionnaire, Core 30, *QLQ-CR29* Quality of Life Questionnaire with diagnosis-specific modules for colorectal cancer, *QLQ-PR25* Quality of Life Questionnaire with diagnosis-specific modules for prostate cancer, *STAI-S* State-Trait Anxiety Inventory – State anxiety subscale.

^1^ = if appropriate.

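### The HADS analysis names neither baseline HADS nor the curability stratum as a covariate, so the 10-month comparison forgoes precision that is already collected

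*Protocol article*

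**What the plan says.** The primary research question asks whether stepped-care participants "report lower levels of anxiety and/or depressive symptoms at 10 months after randomization compared with participants receiving standard care". Table 1 (Data collection) schedules HADS "At baseline and at 1, 4, 7, 10, 18 and 24 months". The same questionnaire decides who is randomised, so every randomised participant has a baseline score.

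On allocation, the Randomization section says: "Randomization will be stratified for curable/non-curable disease and will be done in blocks". The Background treats that factor as prognostic: "Patients with incurable disease report higher levels of anxiety and depression compared with patients who can be cured".

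Data processing and analysis states that group differences in anxiety, depression, post-traumatic stress and quality of life, including their course over time, "will be analysed using analysis of variance (ANOVA) with repeated measurements". Mixed regression models replace this only if normality or equal variance fails. A later sentence in the same section promises control for background variables, medical and socio-demographic ones among them, that might act as moderators or confounders. No variable is named there.

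**The concern.** The question is about one time point, 10 months, and the best available predictor of a patient's 10-month HADS score is likely to be that patient's baseline score. Repeated-measures ANOVA does not use it in that role. There are three ways to read the named model:

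- Baseline is a level of the time factor and the group main effect is tested. The effect is then averaged over all visits, including one at which treatment cannot have acted, and it is not a 10-month difference.
- Baseline is a level of the time factor and the group-by-time term is read at 10 months. That is a change-from-baseline contrast.
- Baseline is left out. Its information is then unused.

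None of these is covariate adjustment. The fallback to mixed models does not settle the matter, because its trigger is distributional and has nothing to do with baseline.

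At stake is precision. Chance baseline imbalance is either left in the 10-month comparison or over-corrected by a change score. Separately, omitting a prognostic stratification factor from the model makes the standard error somewhat too large. Both points hold with complete data.

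**Working it through.** **Inputs from the article (Statistical power).** For anxiety, the design is set out as "To achieve 80% statistical power (alpha = 0.05) needed to detect a mean difference of 2.0 points on the anxiety subscale". The target difference for depression is 1.6 points, and the evaluable number is 65 per group. The differences are 20% of means of 10 and 8, following "A change of at least 20% on the HADS is considered to be a clinically relevant change".

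**Assumptions, not in the article.** Alpha is two-sided. The correlation rho between baseline and 10-month HADS is varied from 0.3 to 0.7. For the change score, the SD is taken as equal at both times.

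**Step 1: the plan's own figure.** No SD is given, so 65 cannot be reproduced from stated inputs alone; it can be back-solved. By the normal approximation, the standardised difference is d = (1.960 + 0.842) × √(2/65) = 0.491. The implied SD is 2.0/0.491 = 4.07 for anxiety and 1.6/0.491 = 3.26 for depression. The exact t calculation gives d = 0.495 (SD 4.04 and 3.23). Both subscales have the same d, so the results below apply to each. An SD of exactly 4.0 or 3.2 (d = 0.5) would need 63 per group (64 by the t-test), close to the stated 65. The figure therefore fits a plain two-group comparison with no baseline adjustment.

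**Step 2: power under three analyses.** The SD of the analysed quantity is:

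- 10-month score alone: SD
- change from baseline: SD × √(2(1 − rho))
- 10-month score adjusted for baseline: SD × √(1 − rho²)

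Power is approximately Φ(2.802/k − 1.960), where k is the multiplier of SD. For rho = 0.3, adjustment gives k = √0.91 = 0.954 and Φ(2.937 − 1.960) = 83.6%. The change score gives k = √1.4 = 1.183 and Φ(2.368 − 1.960) = 65.8%.

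| rho | 10-month score alone | Change from baseline | Adjusted for baseline | Gain of adjustment over 10-month score alone |
|---|---|---|---|---|
| 0.3 | 80.0% | 65.8% | 83.6% | 3.6 points |
| 0.4 | 80.0% | 72.5% | 86.4% | 6.4 points |
| 0.5 | 80.0% | 80.0% | 89.9% | 9.9 points |
| 0.6 | 80.0% | 87.9% | 93.8% | 13.8 points |
| 0.7 | 80.0% | 95.1% | 97.5% | 17.5 points |

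Adjustment is ahead of both alternatives in every row. At rho = 0.5, 80% power would need about 65 × (1 − 0.25) = 49 per group.

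**Step 3: size of chance imbalance.** If the baseline SD is also 4.07, the standard error of the baseline difference at 65 per group is 4.07 × √(2/65) = 0.71 points, against a target difference of 2.0.

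**Step 4: the stratum.** The article gives neither the size of the curable/non-curable difference nor the split between strata, so its contribution cannot be derived. As an illustration only, if the stratum explained 1%, 5% or 10% of the 10-month variance, adjusting for it alone would give 80.4%, 82.0% or 84.0%.

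**The case against.** A reader might infer that the planned analysis adjusts for neither variable. The article does not support that. Curability is a medical factor that the Background links to distress, so it can fall under the sentence on background variables; not naming a covariate in an article is not the same as excluding it. Baseline HADS may also be present as a time level. What stands is narrower: the sentence on background variables does not reach the baseline value of the outcome, and being a time level is not covariate adjustment.

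A reader might also infer that the trial loses about 10 points of power. The 65 per group was sized for 80% without adjustment, so an unadjusted 10-month comparison keeps its planned power. The 10 points are a gain forgone, they arise at an assumed rho of 0.5, and all of them come from baseline HADS. Recruiting on a HADS cut-off narrows the baseline range and may lower rho, and at 0.3 the gain is only 3.6 points. A true shortfall against 80% needs both a change-type contrast and rho below 0.5. The article states neither the contrast nor rho.

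Finally, covariate lists and exact contrasts are commonly left to an analysis plan, which is not shown here. That is fair for the list. But the article is not silent: it commits to a named model, and a better one is available. The named model is valid under randomisation, and leaving out a prognostic stratum tends to make the test conservative, so this is a point about efficiency.

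**Conclusion.** The point holds as a free improvement. The article commits to a model in which baseline HADS is either an outcome level or unused, and it names neither baseline HADS nor the stratum as a covariate. Against 80% for the unadjusted 10-month comparison, adjusting for baseline HADS would give about 84% at rho 0.3, 90% at 0.5 and 97.5% at 0.7, with the lower end the more cautious expectation. Under a change-from-baseline contrast, power would be 66% at rho 0.3 and would reach the planned 80% only at rho 0.5. These figures rest on two-sided alpha, an SD back-solved from 65 per group, and a correlation that the article does not give. No figure can be attached to the stratum. Nothing here makes the planned comparison biased or the sample size wrong.

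**What to change.** State in Data processing and analysis, or in the analysis plan, that the 10-month between-group difference in each HADS subscale is estimated with that subscale's baseline score and the curable/non-curable stratum as covariates. This can be an ANCOVA at 10 months. It can equally be a longitudinal model of post-baseline HADS with treatment, visit, treatment-by-visit, baseline score and stratum, from which the 10-month contrast is read. Baseline should not also appear as an outcome level. Apply the same rule to other outcomes with a baseline value, such as PCL-C, EORTC QLQ-C30, MADRS-S and STAI-S.

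The cost is one sentence and two model degrees of freedom. No new data or patients are needed, and the target of 65 evaluable per group can stay as it is.

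### Mixed models are reserved for failed distributional assumptions, while the default repeated-measures ANOVA, unless data are imputed, is a completers' analysis at odds with the intention-to-treat statement

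*Protocol article*

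**What the plan says.** All references are to the protocol article.

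- **Principle** (Data processing and analysis): "The end points of the study will be evaluated according to the intention-to-treat principle".
- **Main method** (same section): group differences in anxiety, depression, post-traumatic stress and quality of life, and their course over time, "will be analysed using analysis of variance (ANOVA) with repeated measurements".
- **Fallback** (same section): "Should the variables not satisfy the basic assumptions of normal distribution and equal variance, the Mixed regression models will be used for analysis". Missing data are not named as a reason to switch.
- **Time points** (same section): "We will analyse the differences between the groups in the short term, after 1, 4, 7, 10 months, and in the long term, after 18"; the sentence goes on to 24 months.
- **Primary question**: whether stepped-care participants "report lower levels of anxiety and/or depressive symptoms at 10 months after randomization compared with participants receiving standard care".
- **HADS schedule** (Data collection, Table 1): "At baseline and at 1, 4, 7, 10, 18 and 24 months", which is seven waves.
- **Expected loss** (Statistical power): "approximately 30% of study participants will not complete the data collection". For this reason 65 evaluable patients per group become at least 95 included.

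**The concern.** Classical repeated-measures ANOVA needs a value at every wave in the model. A patient who misses one modelled wave contributes nothing, including the waves that were answered. With about 30% expected not to finish, the default method becomes an analysis of completers unless something is done about missing values. That does not fit an intention-to-treat claim.

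The condition for switching does not address this. A standard linear mixed model also assumes normal residuals, so it is no remedy for non-normality. What it offers here is use of incomplete records, valid if missingness is at random given the observed data. Under the stated rule, if HADS scores look normal with equal variances, the trial keeps the method that discards patients. The choice of main method is also settled only once outcome data have been inspected.

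A second, smaller gap concerns the 10-month question. The ANOVA group term averages over waves, and the group-by-time term tests for any difference in profile. Neither is the 10-month difference, and the article does not say which term or contrast answers the primary question.

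At stake is bias in the primary comparison if those who leave differ in distress between arms. This is conceivable: the Discussion says the trial is unblinded, and only the intervention arm has the support material, log-in reminders and the step 2 offer.

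**Working it through.** **1. Reproduce the plan's own figure.** Inputs from Statistical power: 65 evaluable per group, 30% non-completion. 65 / (1 − 0.30) = 92.9, so 93. The article states 95, which agrees to within 2 patients.

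**2. Patients left under complete-record ANOVA.** 95 × 0.70 = 66.5, so about 66 per arm. Left out: 95 × 0.30 = 28.5 per arm, or 190 × 0.30 = 57 of 190 in total.

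**3. Power for a 10-month comparison.** No SD is stated, so it is back-solved from 65 per group, 80% power and alpha 0.05 (two-sided assumed).

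- Standardised difference: d = (1.960 + 0.842) × √(2/65) = 0.491.
- Implied SD: 2.0 / 0.491 = 4.07 (anxiety) and 1.6 / 0.491 = 3.26 (depression).
- Power = Φ(d√(n/2) − 1.960).

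| n per arm | d√(n/2) | Power |
|---|---|---|
| 65 | 2.80 | 0.80 |
| 66 | 2.82 | 0.81 |
| 95 (no loss) | 3.39 | 0.92 |

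The planned loss is therefore already paid for. The 0.92 is an upper bound for a mixed model that also uses the partial records.

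**4. Bias among completers.** This was examined by simulation: 3,000 runs, 95 per arm, waves at 0, 1, 4, 7 and 10 months, equal correlation 0.6, effect growing linearly to 0.49 SD at month 10, and monotone drop-out of about 30%. Log-odds of leaving changed by 0.5 per SD of the previous score. All of these settings are assumptions except the sample size, the wave times, the overall loss and the 0.49 SD derived in step 3.

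| Drop-out pattern | True difference (SD) | Completers (SD) | Likelihood estimate, all randomised (SD) |
|---|---|---|---|
| Unrelated to score | 0.49 | 0.50 | 0.50 |
| Same relation in both arms | 0.49 | 0.49 | 0.49 |
| Opposite relation, high scorers leave intervention | 0.49 | 0.69 | 0.49 |
| Opposite relation, low scorers leave intervention | 0.49 | 0.27 | 0.49 |
| Opposite relations, no true effect | 0 | about 0.20 either way | about 0 |

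In the last row, a nominal 5% test at 10 months in completers rejected in 21–22% of runs. On the implied anxiety SD, 0.20 SD is 0.20 × 4.07 = 0.8 points.

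**5. Which term is tested.** The group-differences sentence covers 10 months as one of six time points. The ANOVA sentence covers levels and development over time. No sentence joins either to the primary question by naming a term or contrast.

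**The case against.** Several points on the other side stand.

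- **Exclusion is not stated.** The article nowhere says that incomplete records will be dropped. Imputation could be specified in an analysis plan that is not shown, and its absence from an article is not a fault. A reader might infer that 30% will be dropped; the documents support only that this follows if ANOVA is used without imputation.
- **Ten months is covered.** A reader might infer that the 10-month difference is never tested. That is too strong, because group differences at 10 months are planned. What remains is that the primary question is not linked to a specific test.
- **Power is protected.** A reader might infer an underpowered trial. Step 3 shows otherwise. Adding further missed visits on top of the 30% risks double counting, since that figure refers to completing data collection as a whole.
- **Half of the trigger is sensible.** Mixed models can allow unequal variances, and the article does not restrict them to normal-theory linear models. The rule is also stated in advance. None of this makes distributional checks the right gate when incomplete records are the foreseeable problem.
- **Bias needs a particular pattern.** It is negligible when drop-out depends on score alike in both arms, and the documents give no evidence of opposite patterns.
- **Covariates.** Leaving baseline HADS or the stratum ("Randomization will be stratified for curable/non-curable disease and will be done in blocks") out of the named model is not an error. The article says background variables will be controlled for, and model detail may sit in the analysis plan.

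**Conclusion.** The concern holds in a limited form. The article selects its main method on the wrong criterion. Its default, taken without imputation, would analyse about 66 of 95 per arm and so conflict with its own intention-to-treat statement. The 66 assumes that every non-completer lacks at least one wave in the model; if only waves up to month 10 enter, patients lost later would stay in.

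The sample size absorbs the loss, with about 81% power against a ceiling of 92% if all 95 were observed. The main harm is therefore possible bias, and its size depends on assumptions. It is close to nil with similar drop-out in both arms. In the assumed opposite-direction scenarios the completer estimate is 0.27 to 0.69 SD against a true 0.49, with a false-positive rate of 21–22%. The secondary harm is that answered visits from patients who later leave go unused. The missing link between the 10-month question and a named contrast is a gap in specification, not evidence that the wrong hypothesis will be tested.

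**What to change.** 1. Make a likelihood-based linear mixed model for repeated measures the primary analysis for each HADS subscale. Include all randomised patients with available data, with arm, visit and arm-by-visit terms and an unstructured covariance.
2. Name the arm difference at 10 months from this model as the primary contrast.
3. Delete the switch based on normality and equal variance. Deal with doubtful distributions by robust standard errors or a bootstrap.
4. Add a sensitivity analysis that lets missing values depart from missing-at-random.
5. Optionally, adjust for baseline HADS and the curable/non-curable stratum. Both are recorded anyway, so this costs nothing.

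The cost is a change of wording, made before outcome data are examined, and a little more analysis work. No extra patients, visits or questionnaires are needed.
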